#### Gastrocnemius Muscle Biopsy

Prior to muscle biopsies, all subjects will be asked to refrain from anticoagulant medications. Samples from the gastrocnemius muscle will be obtained using the Bergstrom percutaneous needle biopsy technique. Biopsy sites will be anesthetized with a 2% Xylocaine solution and a 0.5 cm incision will be made through the skin and fascia. Separate samples will be taken with approximately five passes of the needle into the muscle. All samples will then be prepared immediately by weighing and then dividing the samples for later analysis. A tissue sample of approximately 100 mg is consistently obtained with a triple pass from a single insertion; we have demonstrated that this amount of tissue is sufficient for analyzing muscle fiber composition and angiogenesis. Visible blood and connective tissue will be removed and the specimens divided longitudinally. Portions for RNA (40 mg) analyses will be frozen in liquid nitrogen and stored at -70°C. Another portion to be used for histochemical analysis (~30 mg) will be oriented such that the fibers run longitudinally, mounted on cork-embedding medium (OCT compound), and frozen in isopentane cooled with liquid nitrogen.

For the analysis of the muscle tissue, after thawing the tissue, measurements will be taken for markers of angiogenesis including the following: capillaries per unit area and per muscle fiber, endothelial cells with surrounding pericytes, and relative fraction of type I, IIa, IIb, and IId/x fibers. Additionally, oxidative capacity of the fibers will be quantified via mitochondrial volume with citrate synthase activity.

### Regulatory Issues

Informed consent has been obtained from each patient and the study has been approved by the Duke University School of Medicine Institutional Review Board. The study is being run under an Investigational New Drug application filed with the US Food and Drug Administration.

### Statistical Analysis Plan

This is a repeated-measures design, with the purpose of assessing change over time for the two intervention groups. Since this is a pilot study, the overarching goal of the analyses is to derive effect sizes (ie, effectiveness) for this intervention for a future larger, confirmatory study. We will conduct the analyses chronologically in three phases: (1) descriptive analyses of dependent and independent variables; (2) bivariate analyses of the association between group membership and the outcome measures; and (3) controlled multivariable analyses, which assess the association between groups and the outcomes controlling for important covariates. Randomization should ensure the groups are initially equal; however, we will control for important baseline variables, including the two outcomes of interest. We will not control for any variables observed postrandomization [46]. Our general analytic strategy will be to employ these models to assess differences between groups and, most importantly, assess the differences in change over time between the groups. Our general baseline model will have the following form:

Y
_it_ = β
_0_ + β
_1_ (Group) + β
_2_ (Time
_t_) + β
_3_ (Group × Time
_t_) + β
_4_ (Covariates
_it_) + ε
_it_ (5)

where Y_it_ is the change in the outcome over the time points, t is an indicator of change period (t=2,4) depending on the wave of measurement, and i is an indicator of the individual (i=1,24). β_1_ is an indicator variable indicating group membership. β_2_ is an indicator variable indicating the time of testing: baseline, baseline on supplement, postintervention on supplement, and postintervention off supplement. β_3_ is a Group × Time_t_ interaction. As listed, β_4_ is a vector of regression weights linking the design matrix of covariates—time varying and time invariant—to the outcome of interest. We will center Time_t_=0 at the final 12-week time point, which will allow us to test if there are differences at the end of the trial, β_1_=0. Follow-up analyses will assess the impact of Group × Time_t_ interaction and the functional form of the change over time. Inclusion of covariates into the model, including baseline measures, may add precision to the estimates and allow us to assess the generalizability of the effects across the covariates. The list of covariates (eg, age, gender, health events, comorbidity, and medications) will be developed prior to any analysis. This is a small sample (n=24); hence, the number of covariates we can utilize in any regression is minimal: ≈10 cases per variable [47]. We will assess the impact of each potential covariate individually without respect to group and, if significant (*P*=.10), it will be retained in models with Group, Time_t_, and Group × Time_t_ (see above).

This is a pilot study and we do not expect to declare statistical significance for any of the variables assessed under this analytic structure. However, if the target 12 subjects per group is attained—EX+BR and EX+PL; 24 total subjects—and if a power of 80% with alpha set to .05 (two-tailed) is used, then we will be able to detect a 0.826 standardized difference in the difference in the change labeled as “large” in the statistical power literature [49]. We will not control for the type I error risk inherent in testing multiple outcomes. Rather, should any outcome be declared significant, the reader will be alerted to the number of tests performed and the risk in drawing definitive conclusions with multiple outcomes and a small sample size.

As noted previously, the results from this pilot study will be used to power a subsequent, larger, adequately powered confirmatory clinical trial of the impact of beetroot juice on the outcomes listed above. The results, along with theory and clinical significance, will guide the choice of the primary outcome(s) for that trial, with appropriate control for type I error. While the results of this pilot study will prove useful in the calculation of power, we are aware of the many risks of “playing the winner” in choosing to power a subsequent trial from pilot study results only [50,51].

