### Recruitment Strategies and Eligibility

We aim to recruit a total of 30 participants—equal numbers of men and women—between the ages of 40 and 80 years with diagnosed PAD from the clinics and community at Duke University Medical Center. We anticipate a dropout rate of approximately 15%-20% and, therefore, 24 patients out of the 30 (EX+BR, n=12; EX+PL, n=12) are expected to complete the study. This study will have continuous rolling enrollment until the recruitment goals are met. Subjects will be recruited primarily through collaboration with Duke University Medical Center cardiovascular physicians and vascular surgeons. Clinic medical records will be reviewed to prescreen patients for inclusion and exclusion criteria (see Textbox 1).

Inclusion and exclusion criteria for study screening visit.**Inclusion criteria:**1. Aged between 40 and 80 years.2. Diagnosed peripheral artery disease (ankle-brachial index <0.90) with intermittent claudication.3. No major changes in medications for at least 3 months.**Exclusion criteria:**1. Foot ulcers, advanced neuropathy, gangrene, or other musculoskeletal condition that could limit exercise performance.2. Type 1 diabetes or glycated hemoglobin >8.5%.3. A major cardiovascular event within the previous 6 weeks or a planned hospitalization within the next 2 months.4. Any cardiovascular condition that impacts safety of completing a cardiopulmonary exercise test, including history of significant left main or three-vessel coronary artery disease (>70% stenosis), recent myocardial infarction (6 weeks), chest pain during cardiopulmonary exercise test, or >2 mm ST depression during exercise; foot ulcers/advanced neuropathy or other musculoskeletal condition that could limit exercise performance.5. Allergy to beets or proton pump inhibitors.6. Refusal or inability to abstain from the use of proton pump inhibitors for 24 hours prior to testing.

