## Results

Data collection from this study has been completed and is in the process of analysis and write-up. While the study is too underpowered—EX+BR, n=11; EX+PL, n=13—to determine between-group differences in the primary outcomes of COT, PWT, and 6MW, preliminary observations are promising with Cohen *d* effect sizes of medium to large.

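### The detectable difference of 0.826 does not follow from 12 per group: the stated inputs give about 1.20, and power at 0.826 is about 49%

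*Protocol article*

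**What the plan says.** The Statistical Analysis Plan section of the protocol article makes one quantitative statement about sensitivity. Its conditions are "if the target 12 subjects per group is attained" (24 subjects in total) and "if a power of 80% with alpha set to .05 (two-tailed) is used". Its conclusion is that "we will be able to detect a 0.826 standardized difference in the difference in the change", a size it labels large.

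The section on recruitment and eligibility confirms that 24 is the total across both arms and is already net of dropout: "24 patients out of the 30 (EX+BR, n=12; EX+PL, n=12) are expected to complete the study". The Results section reports the numbers reached as "EX+BR, n=11; EX+PL, n=13".

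The analysis section also plans to control for baseline variables and remarks that covariates may improve precision. It attaches no correlation, R-squared or other variance reduction to the power statement.

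**The concern.** The sample size per group, power, alpha, sidedness and effect scale are all given, so the detectable difference can be recomputed. It does not come out at 0.826. With 12 per group, an effect that size is well short of what can be detected with 80% power.

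A reader is told that the pilot has four chances in five of detecting a difference of 0.826 SD. On the stated inputs the chance is about even. The statement is too optimistic by a factor of 1.197 / 0.826 = 1.45. It matters for reading the pilot, because a non-significant result would look more informative than it is. It also matters for what follows, because the protocol intends the pilot to help power a confirmatory trial. If a total were again used in place of a per-group number, that trial would have half the sample it needs.

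**Working it through.** **Inputs**

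- Per-group size 12, total 24; two-sided alpha 0.05; power 80%; stated effect 0.826 in SD units of change (Statistical Analysis Plan).
- Completers: 12 + 12 = 24 of 30 recruited, which is 30 × (1 − 0.20) (Recruitment Strategies and Eligibility).
- Achieved: 11 and 13 (Results).

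**Method.** Two-sample t-test on change scores, SD of change = 1. For group sizes n1 and n2:

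- degrees of freedom = n1 + n2 − 2
- noncentrality = d / √(1/n1 + 1/n2)
- power = probability that a noncentral t with this noncentrality exceeds the two-sided critical value in absolute size. The detectable d is the value at which this equals 0.80.

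**Reproducing the plan's figure.** With 24 per group, √(2/24) = 0.2887 and df = 46. The detectable d is 0.8261, and power at 0.826 is 79.99%. This matches the printed figure to three decimals, but for 48 subjects.

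**Results across sample sizes**

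| Group sizes | df | √(1/n1 + 1/n2) | Detectable d, 80% power | Power at 0.826 |
|---|---|---|---|---|
| 12 / 12 (planned) | 22 | 0.4082 | 1.197 | 49.0% |
| 11 / 13 (achieved) | 22 | 0.4097 | 1.201 | 48.7% |
| 15 / 15 (all 30, no dropout) | 28 | 0.3651 | 1.060 | 58.9% |
| 24 / 24 | 46 | 0.2887 | 0.8261 | 79.99% |

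Check by normal approximation for 12 per group: (1.960 + 0.842) × 0.4082 = 1.144, with power at 0.826 of 52.5%. The conclusion does not depend on using the t distribution.

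**Other calculations that might have been meant**

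- One-sided alpha 0.05, 12 per group: 1.048 (normal approximation 1.015).
- Paired or one-sample test, n = 12: 0.889 (normal approximation 0.809).
- Paired or one-sample test, n = 24: 0.597.

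None gives 0.826.

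**Variance reduction needed to reach 0.826 with 12 per group.** The SD would have to shrink by 0.826 / 1.197 = 0.690, and the variance by 0.690² = 0.476.

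- ANCOVA on one baseline, variance factor 1 − r²: r = √(1 − 0.476) = 0.72. Allowing for the lost degree of freedom (df = 21, unadjusted detectable d = 1.1995), r = 0.725.
- Change scores divided by the raw-score SD, variance factor 2(1 − r): r = 1 − 0.476/2 = 0.76.

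**Significance threshold and precision, unadjusted t-test.** The critical value at df = 22 is 2.074. The smallest significant observed d is 2.074 × 0.4082 = 0.847 at 12/12 and 2.074 × 0.4097 = 0.850 at 11/13. At 11/13 an observed d of 0.5 has a 95% CI of −0.32 to 1.31, a half-width of about 0.8 SD.

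**The case against.** The strongest defence is that the planned analysis is not an unadjusted t-test. The model uses repeated measures and baseline covariates, and there are four assessment points. Under equal correlation between time points and scaling by the raw-score SD, more modest correlations would reach 0.826 with 12 per group:

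- ANCOVA on the mean of two post-training measures, variance factor (1 + r)/2 − r²: r = 0.54 gives 0.770 − 0.292 = 0.478, close to the 0.476 needed.
- Two pre and two post measures compared as means, variance factor 1 − r: r = 0.52 gives 0.48. This route is weaker, because the second assessment is already on supplement.

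A condensed article might also leave such an assumption to a fuller document. What stands is that 0.826 cannot be called impossible with 12 per group under every analysis, and that the reason for the discrepancy is not proven. What does not stand is the figure as printed. The sentence states no variance reduction and expresses the effect as a standardized difference in change, whereas these routes scale by the raw-score SD. An exact match to 24 per group is also more simply explained by a substituted sample size.

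The second defence is that this is a pilot. The plan does not expect significance, makes effect-size estimation its goal, warns against choosing a later primary outcome on pilot results alone, and in the Results section admits that it is underpowered. The sample size was not derived from 0.826, and the label large fits 1.20 equally well. All of this stands and limits the consequence, but it does not make the number right.

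A reader might go further and infer that the effects described in the Results section ("preliminary observations are promising with Cohen *d* effect sizes of medium to large") all have intervals that include zero. The document does not support that. It gives no d values or intervals, and a large effect may lie above 0.85. Nor does it follow that an observed d below 0.85 could not be significant in the planned analysis: that threshold is for the unadjusted t-test, and adjustment could lower it.

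**Conclusion.** The sensitivity statement is wrong as written. On its own inputs the detectable standardized difference in change is about 1.20 (1.197 for 12/12, 1.201 for 11/13), and power at 0.826 is about 49%. This rests on a two-sample t comparison of change scores, standardized by the SD of change, with no variance reduction, which is the calculation that the sentence describes. That the total of 24 was entered as the per-group size is the likely cause and no more than that.

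The conclusion is confined to this figure. It says nothing about the unreported effect sizes in the Results section, and whether to call them promising is the authors' judgement, which this error does not settle.

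**What to change.** Replace the sentence with, for example: *With 12 per group, 80% power and two-sided alpha .05, the detectable standardized difference in change is about 1.20; power for 0.826 is about 49%.* Alternatively, if a correlation or covariate adjustment lay behind 0.826, state it, name the SD used for scaling, and show the resulting calculation.

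Because the stated goal is to estimate effect sizes, the expected precision can usefully be given alongside: a 95% CI half-width of about 0.8 SD for an unadjusted comparison.

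The cost is wording only. Design, data and analysis do not change. The one drawback is that the stated sensitivity becomes less favourable.

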## Results

Data collection from this study has been completed and is in the process of analysis and write-up. While the study is too underpowered—EX+BR, n=11; EX+PL, n=13—to determine between-group differences in the primary outcomes of COT, PWT, and 6MW, preliminary observations are promising with Cohen *d* effect sizes of medium to large.

## Discussion

### Principal Findings

Improving pain-free walking and exercise capacity are key goals for the treatment and rehabilitation of patients with peripheral arterial disease [1]. This study aims to determine if the combined intervention of the current best treatment for PAD (ie, supervised exercise training) in conjunction with inorganic nitrate supplementation using beetroot juice can increase exercise tolerance more than exercise training alone (ie, placebo supplement).

The physiological basis for this trial relies on the fact that supplementation with inorganic nitrate will lead to increased plasma nitrite that can be transported throughout the circulation and is reduced to NO in tissue with a low partial pressure of oxygen. This hypoxic tissue-targeting effect may be particularly pertinent for patients with PAD+IC experiencing tissue ischemia during exercise participation. While it is well established that consuming inorganic nitrate increases circulating levels of plasma nitrite [28,52], research on the corresponding effect on key clinical outcomes such as exercise performance in clinical patients, while promising, is still limited [27,38,39].

There are three mechanisms that lend support to nitrate supplementations’ clinical utility in improving exercise performance in patients with PAD. First, acute supplementation data suggest that increasing plasma nitrite via beetroot juice improves ischemic tissue perfusion leading to increases in pain-free walking time and aerobic function [27]. Second, increased exercise time or intensity will facilitate greater training responses and tissue adaptations. Third, increased bioavailability of NO could lead to a greater tissue angiogenic response. These mechanisms are complementary to each other and may result in a greater overall exercise tolerance

### Study Limitations

The small sample size and the focus on patients with PAD+IC only limit the ability to broadly apply the results of the study to the larger PAD population and to generalize these results to subsequent studies. This study also uses a per-protocol design with the intent that data may provide the physiological proof of concept for the intervention and allow us to derive variance data and effect sizes within and between groups to inform future studies, which will utilize an intent-to-treat criterion in the analytic structure.

### Potential Impact

This study has been designed to investigate a new therapeutic approach for the treatment of PAD+IC. If successful, the results could influence current medical practice for these patients, while also providing mechanistic insights into potential physiologic targets for other interventions. Research clearly identifies supervised exercise training as being one of the most effective interventions for improving exercise tolerance in patients with PAD [1,53,54]. We hypothesize the combination of supplementation with exercise will create greater adaptations than the sum of the individual exposures alone. If true, the findings would lead to a paradigm shift in the treatment recommendations for patients with PAD.

## Abbreviations

6MW: 6-minute walk
ABI: ankle-brachial index
AIx: augmentation index
AT: anterior tibial
BP: blood pressure
BR: beetroot
COT: claudication onset time
CPX: cardiopulmonary exercise test
ΔP: pressure augmentation
DP: dorsalis pedis
DPW: distance of pulse wave
EX+BR: exercise training plus beetroot juice
EX+PL: exercise training plus placebo juice
Hb: hemoglobin
IC: intermittent claudication
max CPX: maximal-graded cardiopulmonary exercise test
NIRS: near-infrared spectroscopy
NO: nitric oxide
NO2-: nitrite
NO3-: nitrate
PAD: peripheral artery disease
PAD+IC: peripheral artery disease with intermittent claudication
PL: placebo
PT: posterior tibialis
PWT: peak walk time
PWV: pulse wave velocity
VO _2peak_: peak oxygen uptake

## Appendix

Multimedia Appendix 1 NIH Clinical and Integrative Cardiovascular Sciences Study Section: Peer review report.
